## Methods

### Study setting

Recruitment will take place in urology and radiation oncology clinics at participating sites in the True NTH consortium: University of Michigan, Emory University, Johns Hopkins University, University of California –Los Angeles and Memorial Sloan Kettering Cancer Center. Sites were selected based on (1) patient volume which will impact feasibility and recruitment costs, (2) diversity of the patient population, and (3) current standard of care regarding sexual health. Each site will have a site PI and a study coordinator. The website’s survey and intervention couple engagement logistics data will be centrally managed at the University of Michigan which will also serve as the coordinating site for clinical data and a provider of technical support for all participating sites. Potential participants will be identified by a member of the study team at participating sites through screening clinic and surgical schedules as well through referral by the treating physician. The goal for each site will be to recruit a minimum of 15 couples and a maximum of 50 couples.

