### Randomization

The patient/partner dyad will be randomized to either the intervention arm or the usual care arm after completion of the informed consents, and prior to initiation of treatment. Randomization will be performed using a computer-generated randomized block design to minimize the potential for sample size differences between the two arms. The randomized block design will be stratified by enrollment site to facilitate ease of administration of the trial (Fig. 2). Participants randomized to usual care will be routed to the American Cancer Society’s web page that provides information about the sexual side-effects of cancer and sexual rehabilitation, which can be considered a part of usual care. Participants will be blinded as to the arm that they are entering by language at recruitment which will indicate that we are comparing two supportive interventions for sexual recovery after prostate cancer treatment. Participants will be unblinded by letter after they complete their 6-month survey.

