### Analysis

The primary endpoint of PROMIS Satisfaction with Sex Life at 6 months is expected to be a continuous measurement that is normally distributed. If not, we will transform the data for this outcome to approximate normality. Since the primary outcome is measured on both patients and partners and randomization was done at the level of each dyad, we will assess the impact of the intervention using the Actor-Partner Interaction Model (APIM) [59]. The APIM is a mixed-effects linear regression model that allows us to simultaneously estimate the association of partner characteristics with partner and patient outcomes, as well as simultaneously estimate the association of patient characteristics with both outcomes. The APIM incorporates random effects to account for the correlation between patient and partner outcomes from the same dyad. Our base model will contain (1) an indicator of intervention versus control, (2) baseline PROMIS Satisfaction with Sex Life, (3) a indicator of partner versus patient, (4) interaction terms of (3) with (1) and (2), (5) a random partner effect to account for variation among partners, (6) a random patient effect to account for variation among patients, and (7) a third random effect to account for the correlation (non-independence) between outcomes measured from the same dyad. From this base model, we can assess not only the relative impact of the intervention among dyads, but also the differential impact of the intervention on partners and partners.

We can then expand our base model to include other partner characteristics and/or patient characteristics to assess whether or not these characteristics moderate or mediate the effect of the intervention for the patient and the partner. For example, we could include baseline satisfaction with sex life of the partner and the patient and see if either or both factors moderate or mediate the effect of the intervention on 6-month satisfaction with sex life. We note that because dyads were randomized to the intervention, we expect dyad level characteristics to have little effect in our model because those factors should be nearly balanced among the two treatment arms. Thus, adjustment for them is unnecessary, except to gain statistical power. The random effects will allow us to estimate the remaining variability of outcomes among partners, among patients, and the correlation of outcomes within each dyad, that is not explained by our APIM.

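### Randomisation is stratified by site but the base model has no site term: if site is prognostic, standard errors are too large and attainable power is forgone

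*Protocol article*

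**What the plan says.** Protocol article, Randomization: the unit is the couple ("The patient/partner dyad will be randomized to either the intervention arm or the usual care arm"), and "The randomized block design will be stratified by enrollment site to facilitate ease of administration of the trial".

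Study setting: there are five sites, and "The goal for each site will be to recruit a minimum of 15 couples and a maximum of 50 couples". Besides patient volume, the site selection criteria were "2) diversity of the patient population, and (3) current standard of care regarding sexual health".

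Analysis: the terms are numbered, and the list opens: "Our base model will contain (1) an indicator of intervention versus control, (2) baseline PROMIS Satisfaction with Sex Life, (3) a indicator of partner versus" (the third term contrasts the two roles). It goes on to the interactions of role with arm and with baseline, a random effect for each role, and "a third random effect to account for the correlation (non-independence) between outcomes measured from the same dyad". Site appears neither as a fixed nor as a random effect. The section then applies the same model to all secondary endpoints.

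On adjustment, the same section says "we expect dyad level characteristics to have little effect in our model because those factors should be nearly balanced among the two treatment arms". The sentence that follows concedes one exception: "Thus, adjustment for them is unnecessary, except to gain statistical power".

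Power calculations: 128 dyads give 80% power at the two-sided 5% level by a t-test, for means of 50 against 45 with SD 10. The recruitment target is 140 dyads.

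**The concern.** The analysis does not follow the randomisation. Blocking within site holds the arms nearly equal at each site, so differences between sites largely cancel out of the arm contrast. A model without site does not know this and still counts between-site variance as random error. The dyad random effect is no substitute. Arm varies between dyads, so any site variance absorbed into that component goes straight into the standard error of the arm effect.

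The protocol's general remark on adjustment does not cover this case. Balance is an argument about bias. It says nothing about how much outcome variance a factor explains, and for a stratification factor it is the forced balance itself that makes an unadjusted standard error too large.

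Site could plausibly matter here. Patient diversity and existing sexual-health care were both considered in choosing sites, the comparator is usual care, and the outcome is sexual satisfaction. At stake are confidence intervals wider than they need be, a test run below its nominal 5%, and some power left unused.

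**Working it through.** **Inputs from the protocol.** Difference 5, SD 10, two-sided 5%, 80% power, 128 dyads, so 64 per arm (Power calculations). Five sites, stratified blocks (Study setting, Randomization).

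**Assumed.** ρ, the share of outcome variance due to site, from 0 to 0.20. The documents give no figure.

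**Step 1: reproduce the plan's figure.** By the normal approximation, n per arm = 2 × 10² × (1.960 + 0.842)² / 5² = 62.8, so 63. The t-test gives 63.8, so 64 per arm and 128 in total, as stated. Power at 64 per arm is 80.1% by the t-test and 80.7% by the normal approximation used below.

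**Step 2: formulas, one role (patient or partner) at a time.**
- Standard error reported without site: SE_rep = √(2 × 100 / 64) = 1.768.
- True standard error under site-stratified allocation: SE_true = √(2 × 100 × (1 − ρ) / 64).
- Type I error without site = 2 × [1 − Φ(1.96 × SE_rep / SE_true)].
- Power without site = Φ((5 − 1.96 × SE_rep) / SE_true).
- Power with site = Φ(5 / SE_true − 1.96).

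Example at ρ = 0.10: SE_true = √(180 / 64) = 1.677 and the ratio is 1.768 / 1.677 = 1.054. Power without site = Φ((5 − 3.465) / 1.677) = Φ(0.915) = 82.0%. Power with site = Φ(2.981 − 1.96) = Φ(1.021) = 84.7%.

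**Step 3: results.**

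| ρ | SE_true | Reported SE too large by | Type I error without site | Power without site | Power with site |
|---|---|---|---|---|---|
| 0 | 1.768 | 0% | 5.0% | 80.7% | 80.7% |
| 0.02 | 1.750 | 1.0% | 4.8% | 81.0% | 81.5% |
| 0.05 | 1.723 | 2.6% | 4.4% | 81.4% | 82.7% |
| 0.10 | 1.677 | 5.4% | 3.9% | 82.0% | 84.7% |
| 0.20 | 1.581 | 11.8% | 2.8% | 83.4% | 88.5% |

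Total SD is held at 10, so a larger ρ means a smaller true error. That is why power rises even without site, though by less than with it.

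**Step 4: allow for baseline satisfaction, which is already in the model.** If baseline explains an assumed 25% of variance and ρ is the site share of what remains, the standard-error excess is unchanged. Power without and with site is then 91.0% and 91.8% (ρ = 0.05), 91.6% and 93.1% (0.10), and 92.8% and 95.5% (0.20). The gain from adding site is roughly halved.

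**Step 5: simulation.** Five sites of 16, 20, 24, 28 and 40 dyads, equal permuted allocation within site, 6000 runs per setting, no baseline covariate.

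| ρ | Type I error without / with site | Power without / with site |
|---|---|---|
| 0 | 4.8% / 4.9% | 81.1% / 81.0% |
| 0.05 | 4.1% / 4.7% | 80.0% / 81.2% |
| 0.10 | 3.9% / 5.1% | 81.3% / 83.9% |
| 0.20 | 3.0% / 5.8% | 82.9% / 88.1% |

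At ρ = 0.10 with the 5-point effect, the mean reported standard error without site was 1.767 against an empirical SD of 1.691. Monte Carlo error for a 5% rate is √(0.05 × 0.95 / 6000) = 0.28 points. The 5.8% with site at ρ = 0.20 is therefore 2.8 Monte Carlo errors above nominal. With normal errors and fixed site effects the adjusted t-test is exact at 5%, so I treat that as simulation noise and rest nothing on it. Direction and scale agree with Step 3.

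**The case against.** Several points on the other side are fair.

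- **The quoted rationale is not about site.** It concerns dyad-level characteristics in general, in a paragraph on expanding the model. A reader might infer that site was left out because of it; the protocol does not say so. Read generously, little effect in the model may mean little effect on the arm comparison, which is correct.
- **The power gain is conceded.** The next sentence allows that adjustment can raise power, so the plan does not overlook precision. This stands. What the concession misses is that for the stratification factor adjustment also corrects the standard error.
- **The effect is conditional.** If site explains little beyond baseline satisfaction, almost nothing changes: at ρ = 0.02 the gap is about half a power point. This stands.
- **Planned power is safe.** A reader might infer that the trial falls short of its 80%. It does not, because that figure comes from an unadjusted t-test and omitting site does not take power below it.
- **Other covariates.** A reader might extend the point to treatment type and baseline sexual function. The extension fails, because these are not stratification factors and omitting them does not make the standard error invalid. FSFI and IIEF are also different instruments, used for female and male partners respectively, and a patient/partner role term does not separate them.
- **This is an article, and the analysis plan is not shown.** The model may be refined there. But the article fixes a numbered list of terms, so this is a stated choice and not an omitted detail.

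**Conclusion.** The point holds in conditional form. Randomisation is stratified by site and the stated model for primary and secondary endpoints ignores site. If site is prognostic beyond baseline satisfaction, standard errors are overstated, the test is conservative, and power is forgone relative to a site-adjusted model. Over an assumed site share of 0% to 20%, the standard error is 0% to 11.8% too large, type I error lies between 5.0% and 2.8%, and the power forgone is 0 to 5.1 points (about 1.3 points at a 5% share).

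The documents do not support a claim of bias, of type I inflation, or of a trial powered below plan, and the required sample size does not rise. The figures take one role at a time with 64 dyads per arm and SD 10. The joint dyadic model would change their size but not their direction. This is a worthwhile, free improvement and not a threat to the validity of the trial.

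**What to change.** Add enrolment site as a fixed effect to the base model, for the primary endpoint and for all secondary endpoints that use the same model. With five sites this costs 4 degrees of freedom, and site is already known for every dyad.

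Reword the sentence on balance along these lines: randomisation and balance address bias; adjustment addresses precision and, for the stratification factor, is also needed for correct standard errors.

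Treatment type and baseline sexual function may be considered as optional covariates for precision, but they are not part of this fix. No change to sample size or data collection is needed. If the analysis plan already contains a site term, only the published text needs to be brought into line.

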### Power calculations

Basing power calculation on the average adjusted PROMIS Satisfaction with Sex Life score of 50 (standard deviation = 10) provided in the PROMIS scoring and anticipating Sexual Satisfaction scores for the intervention group vs. control group to be 50 vs. 45 based on expert opinion, a sample size of 128 patients and 128 spouse/partners will provide 80% power at the 5% significance level to detect this difference using a two-tailed t-test. Adding 10%, or 14 dyads (including an extra one to get to an even number to allow the same sample size in each arm), to our total to account for the anticipated dyads that will be lost to follow-up prior to study completion, we will recruit 140 dyads (280 individuals) for this study (expected to be 70 couples on each study arm).

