**Methods:**

The study team developed an interactive, web-based intervention, tailored to type of treatment received, relationship status (partnered/non-partnered) and sexual orientation. It consists of 10 modules, six follow the trajectory of the illness and four are theme based. They address sexual side effects, rehabilitation, psychological impacts and coaching for self-efficacy.

Each includes a video to engage participants, psychoeducation and activities completed by participants on the web. Tailored strategies for identified concerns are sent by email after each module. Six of these modules will be tested in a randomized controlled trial and compared to usual care. Men with localized prostate cancer with partners will be recruited from five academic medical centers. These couples (*N* = 140) will be assessed prior to treatment, then 3 months and 6 months after treatment. The primary outcome will be the survivors’ and partners’ Global Satisfaction with Sex Life, assessed by a Patient Reported Outcome Measure Information Systems (PROMIS) measure. Secondary outcomes will include interest in sex, sexual activity, use of sexual aids, dyadic coping, knowledge about sexual recovery, grief about the loss of sexual function, and quality of life. The impact of the intervention on the couple will be assessed using the Actor-Partner Interaction Model, a mixed-effects linear regression model able to estimate both the association of partner characteristics with partner and patient outcomes and the association of patient characteristics with both outcomes.

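### The sample-size figures do not reconcile: 128 dyads plus 14 is 142, not 140, and 140 dyads less 10% leave 126; the effect on power is negligible

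*Protocol article*

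**What the plan says.** All of the derivation stands in the Power calculations section of the Protocol article.

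- **Effect and variability.** The expected means are given by "anticipating Sexual Satisfaction scores for the intervention group vs. control group to be 50 vs. 45 based on expert opinion", against an "average adjusted PROMIS Satisfaction with Sex Life score of 50 (standard deviation = 10").
- **Requirement.** The number needed is "a sample size of 128 patients and 128 spouse/partners". That is 128 dyads, 64 per arm. The section sizes this for 80% power with a two-sided t-test at the 5% level.
- **Allowance.** "Adding 10%, or 14 dyads (including an extra one to get to an even number to allow the same sample size in each arm"), and the purpose is "to account for the anticipated dyads that will be lost to follow-up prior to study completion".
- **Target.** "we will recruit 140 dyads (280 individuals) for this study", expected to split into 70 couples per arm. The Methods part of the Abstract gives the same N of 140 couples.

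**The concern.** The section sets out a short sum: a requirement, an allowance and a target. The target is not the sum of the other two. The 14 does not look like a stray digit, because the sentence explains how it arises: 10% rounded up, plus one dyad to make the total even. Yet 140 is only 12 above 128.

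At stake is whether the planned number is 140 or 142, and how much loss it tolerates. Sites and ethics boards work to the recruitment target, and the trial report will have to reproduce its derivation. As printed, a reader cannot do so, and the implied statement that 140 covers 10% loss while keeping 128 evaluable dyads is not true.

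**Working it through.** **Inputs** (all from Power calculations): difference 50 − 45 = 5; SD 10; two-sided 5% level; power 80%; two-sample t-test; equal arms; loss 10%; target 140 dyads.

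**1. Reproduce the requirement.** Standardised effect d = 5/10 = 0.5. Solving the two-sample t-test (noncentral t) for 80% power gives 63.77 per arm, so 64 per arm and 2 × 64 = 128. Power at 64 per arm is 80.1%. The stated 128 is reproduced.

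**2. Reproduce the allowance.** 128 × 0.10 = 12.8, rounded up to 13, plus one for evenness = 14. The stated 14 is reproduced.

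**3. Add them.** 128 + 14 = 142 (71 per arm). The stated 140 is not reproduced; it adds 140 − 128 = 12, which is 12/128 = 9.4%.

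**4. Try the usual ways of allowing for 10% loss, starting from 128.**

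| Rule | Result | Made even |
|---|---|---|
| N × 1.10 | 140.8, so 141 | 142 |
| N / 0.90 | 142.2, so 143 | 144 |

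Neither gives 140.

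**5. What each target leaves after 10% loss.**

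| Recruited | Evaluable (× 0.90) | Against 128 |
|---|---|---|
| 140 | 126.0 | 2 short |
| 142 | 127.8 | 0.2 short |
| 144 | 129.6 | met |

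**6. Power at 126.** With 63 per arm and d = 0.5, t-test power is 79.5%, against 80.1% at 64 per arm: a difference of 0.6 points.

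**7. Loss that 140 can absorb.** (140 − 128)/140 = 12/140 = 8.6%.

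**8. Could 128 be the misprint?** The normal approximation gives n = 2(1.96 + 0.84)²/0.5² ≈ 62.8, so 63 per arm and 126 in total. Then 10% is 12.6, rounded up to 13; plus one is 14; and 126 + 14 = 140. This fits the 14, the extra dyad and the 140, but not the printed 128 or the named t-test. It is an inference; the document does not mention 126.

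**The case against.** The strongest reply is that nothing of substance follows, and most of it stands.

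- **Precision.** The document gives power as a whole percentage, and 79.5% (0.7952) rounds to 80%.
- **The planned analysis is not a t-test.** The Analysis section fits a dyadic mixed model that includes baseline satisfaction. The documents give no correlation r between baseline and 6-month scores, so r has to be assumed. Scaling the SD by √(1 − r²) at 63 per arm, t-test power is 79.9% at r = 0.1, 80.1% at r = 0.12, 83.1% at r = 0.3 and 89.5% at r = 0.5. Any r of about 0.12 or more makes up the difference.
- **The inflation rule.** Adding 10% of the evaluable number is a common convention, and 128 × 1.10 = 140.8 lies within one dyad of 140. Dividing by 0.90 is the stricter rule, but the choice between them moves the target by only about 2 dyads.
- **Source of the slip.** If the base was 126, then 14 and 140 are both right and 128 is the misprint. Deleting the 14 would then correct the wrong number.

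These points limit the consequence and the remedy. They do not remove the inconsistency: whichever number is wrong, 128, 14 and 140 are printed as one sum and do not add up. Nor is this a matter of an article condensing a fuller protocol. The calculation is printed, and the printed figures conflict.

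A reader might infer that the trial is underpowered, or that it must recruit 142 or 144 dyads. The documents do not support that. The shortfall is 2 dyads and about 0.6 points of power under a planning test that makes no use of the baseline score.

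**Conclusion.** The point holds as an internal arithmetic error. The required, added and recruited numbers cannot all be right. Under the section's own 10% loss, 140 dyads leave 126 (63 per arm), 2 below the stated 128, with power 79.5% instead of 80.1%. The target keeps 128 only up to 8.6% loss.

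The size is negligible for the design. The figures rest on the stated inputs (5 points, SD 10, two-tailed 5% t-test applied to one member of each dyad, equal arms) and on loss falling equally on both arms. Which figure is misprinted, 128 or 14, cannot be settled from the document.

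**What to change.** Keep the target of 140. Check the three numbers against the sponsor's own calculation to find out whether 128 or 14 is misprinted. Then rewrite the whole sentence, including the parenthesis about the extra dyad, which would have nothing to refer to if only the 14 were removed. Suggested content:

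> We will recruit 140 dyads (70 per arm). This retains 128 evaluable dyads if loss to follow-up is at most 8.6%. At 10% loss, 126 evaluable dyads (63 per arm) give 79.5% power to detect 5 points (SD 10) with an unadjusted two-tailed t-test at the 5% level.

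If the check shows that the base was 126 by the normal approximation, the text should say so and give that base and method in place of 128 and the t-test.

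The cost is one sentence and a power figure that is slightly less favourable. Recruitment, design and analysis do not change.

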### Ethics

The study will be coordinated by the University of Michigan, the protocol has been approved by the University of Michigan Institutional Review Board (IRB) and by the IRBs of all the other participating sites. The process of the study and protocol modifications, if needed, will be discussed in weekly meetings with all the sites and amendments filed to each institution’s IRB. Data will be collected by the University of Michigan Center for Healthcare Communications Research (CHCR) and stored securely on virtualized servers with a robust back up system. All participants must sign informed consent before enrolling in the study.

## Discussion

Building on the acceptability of a previous web-based intervention for couples after prostate cancer treatment, which was shown to be as effective as a face-to-face intervention [20], our intervention represents several innovations. It is based on an evidence-based theoretical model that incorporates both a biopsychosocial approach to sexuality and the grief process, as a path to recovery. Unlike any previous sexual health intervention, it is interactive and has a personalized approach achieved through tailoring to treatment, partnership and sexual orientation. When fully implemented, it will provide support for men with prostate cancer and their partners along the trajectory of the illness, including during disease progression and in the metastatic stage. This approach recognizes both the hard work that men and couples undertake when they desire to maintain their sexual viability after prostate cancer treatment, and the fact that men and partners benefit from staying close during all phases of illness. [60] Patients’ and partners’ quest to maintain sexual intimacy will be reinforced by modules that provide coaching for discussions of sexual concerns between the patient, partner and healthcare provider and alert them to barriers to sexual recovery with relevant strategies.

The evaluation of the intervention is also innovative. In particular, we are investigating satisfaction with sex life, which may be applicable to a broad array of men, including older men and their partners who may be able to attain/maintain satisfaction with their sex life despite compromised sexual function [61]. Furthermore, the study includes many variables that are critical and relevant to a successful sexual recovery, such as sexual function, grief about the loss of sexual function, dyadic coping, knowledge acquisition, some of which have been primary outcomes in previous studies. Finally, our analytic approach allows us to evaluate the couple which experiences prostate cancer as a unit with reciprocal influence on each other’s outcomes. Our goal is to provide an accessible, comprehensive and individually relevant supportive structure for recovery from this well-recognized long-term treatment effect [62], and to contribute positively to patients’ and partners’ quality of life in survivorship. When the study is completed, we plan to publish the findings. Subsequently, the intervention will be modified, as needed, based on study findings and offered in full on the Movember Foundation-True NTH website to all prostate cancer survivors and their partners.

